## 16. END OF TRIAL DEFINITION

The end of trial will be the date the overall survival and lung cancer data of the last subject has been collected. The Sponsor will notify relevant regulatory authorities and ethics committees that the trial has ended at the appropriate time and will provide them with a summary of the clinical trial report within 12 months of the end of trial.

The Sponsor reserves the right to stop the trial at any time on the basis of new information regarding safety or efficacy (e.g., discovery of an unexpected, significant or unacceptable risk to the subjects enrolled in the trial), or if trial progress is unsatisfactory (e.g., failure to enroll subjects at an acceptable rate), or for other valid reasons (e.g., Sponsor decides to suspend or discontinue development of the drug). After such a decision is made, the Investigator must inform all on-trial subjects within one (1) week. All delivered trial materials must be collected and all e-CRF pages completed to the extent possible.

## 17. STATISTICAL CONSIDERATIONS

### 17.1 Trial Population

The trial subject population includes patients who have marked smoking history and are current smokers and who adhere to the trial inclusion and exclusion criteria.

For the purpose of analyses the following populations are defined:

Efficacy evaluable population – Includes all randomized and undergone at least one round LDCT screening.

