### Intervention Schedule

The intervention period will initiate from randomization. At the randomization visit, all patients will be given written smoking cessation material and blood samples will be collected for biomarker analysis. The patients randomized to intervention arm will be given access to smartphone-based smoking cessation application with user training. The LDCT will be scheduled preferably within six weeks of randomization. After the LDCT, the patient will be informed of the results by mail. If no further procedures are required,

next LDCT will be scheduled for 1y +/- two months). With intermediate LDCT results, follow-up scan will be ordered at three months. With positive LDCT results, the patient will be referred to pulmonologist. At three and six months (+/- one month) after randomization, patient is called to evaluate whether they are active smokers and if they have quit, what is the date of smoking cessation. After the second round LDCT, the subject is scheduled a study visit in which LDCT results are communicated to the subject. In the case of negative LDCT results, patient enters survival follow-up. With intermediate results, new LDCT will be ordered at 2 or 12 months, and positive results will result in referral to pulmonologist. The survival follow-up period can last up to 3 years from inclusion.

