## 6. TRIAL ENTRY

Once the subject has signed informed consent, a subject number will be assigned. After the eligibility check and the enrolment confirmation, any change in the subject eligibility criteria needs to be reported in the CRF and the suitability of the subject to enter the study treatment must be carefully evaluated by the investigator. Once assigned, the subject numbers for any screening failures non-evaluable, or discontinued subjects will not be re-used. Intend-to-treat (ITT) population will be characterized by subject who fulfill the inclusion and exclusion criteria and receive smoking cessation intervention in form of either written material or mobile application.

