### 7.3 LDCT

All the study subjects will undergo LDCT screening within six weeks of randomization. After the LDCT, the patient will be informed of the results by mail. If no further procedures are required, next LDCT will be scheduled for 1y +/- two months). With intermediate LDCT results, follow-up scan will be ordered at three months. With positive LDCT results, the patient will be referred to pulmonologist. After the second round LDCT, the subject is scheduled a study visit in which LDCT results are communicated to the subject. In the case of negative LDCT results, patient enter survival follow-up. With intermediate results, new LDCT will be ordered at 2 or 12months, and positive results will result in referral to pulmonologist. Nodule detection algorithm is presented in Figure 3.

Radiation exposure of single LDCT (effective dose) is 1.6-2.4 mSv, which corresponds to about ½-1v background radiation exposure. During its lifetime, humans are exposed to ionizing radiation from both

natural and artificial sources and the average effective dose received by Finns in 2018 is 5.9 mSv, of which about two thirds (4 mSv) is caused by radon. The additional risk caused by radiation from CT scans performed during the study, ie the risk of cancer, is low. Randomized evidence suggest that annual LDCT in the investigated population decreases lung cancer and all cause mortality and therefore benefits of LDCT clearly outweigh the potential harms.

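### The protocol defines no all-randomised analysis set: section 17.1 requires a post-randomisation LDCT, the section 6 ITT is restricted, and neither is assigned to the smoking comparison

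*Protocol*

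**What the plan says.** Protocol section 17.1 introduces its sets in the plural, "For the purpose of analyses the following populations are defined", but lists one, the efficacy evaluable population, which "Includes all randomized and undergone at least one round LDCT screening". The primary outcomes follow in section 17.2.1 (percentage actively smoking at 3 and at 6 months, by arm), with no population named. Section 17.3 deals only with the timing of analyses.

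A second set stands in section 6: "Intend-to-treat (ITT) population will be characterized by subject who fulfill the inclusion and exclusion criteria" and who "receive smoking cessation intervention in form of either written material or mobile application". Section 17 does not mention it.

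On timing, section 7.3 states "All the study subjects will undergo LDCT screening within six weeks of randomization", and the Intervention Schedule in the summary is softer: "The LDCT will be scheduled preferably within six weeks of randomization". The same schedule gives every subject the written material at the randomisation visit, and gives the app arm access and training with it. Section 7.2.1 obtains smoking status by telephone at 3 and 6 months.

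**The concern.** The primary question is a comparison of two randomised arms, and randomisation protects it only while the arms are analysed as randomised. Attendance at the first scan happens after allocation, and by then a subject knows whether he or she has the app. It may depend on the arm and on motivation to quit. A set conditional on attendance is therefore selected after randomisation by something that may be related to the outcome.

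The condition is also unnecessary. A subject who skips the scan but answers both calls has complete primary data and would still fall outside the only efficacy set. That discards observed outcomes; it is not a missing-data problem. The ITT label in section 6 does not repair this, because that set is also defined by more than allocation, it differs from the 17.1 set, and nothing says which of the two governs.

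**Working it through.** **1. The plan's own figure.** Section 17.2.1: 75% versus 90% smokers, 80% power, 90% confidence, 155 subjects, raised to 200 for dropout. Read as two-sided alpha 0.10, with z-values 1.645 and 0.842:

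- Unpooled: n = (1.645 + 0.842)² × (0.75×0.25 + 0.90×0.10) / 0.15² = 76.3, so 77 per arm, 154 in total.
- Pooled variance under the null: 79 per arm, 158 in total.

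The stated 155 is reproduced. The point concerns who is analysed, not the sample size. The implied overall dropout is 1 − 155/200 = 22.5%.

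**2. The sets side by side.**

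| Set | Condition beyond randomisation | Who could be lost |
|---|---|---|
| Section 17.1 | at least one LDCT | anyone who misses the scan, even with smoking status known |
| Section 6 ITT | eligible, and received written material or app | subjects later found ineligible; almost no one through the receipt condition |
| All randomised, as allocated | none | not defined anywhere |

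**3. Equal exclusion with a true effect.** Assume a fraction d of each arm is excluded and all of them smoke. The analysed rate is (p − d)/(1 − d), and the difference is 0.15/(1 − d).

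- d = 5%: 73.7% versus 89.5%, difference 15.8 points.
- d = 10%: 72.2% versus 88.9%, difference 16.7 points.

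**4. Unequal exclusion with a true effect.** 100 per arm, all excluded subjects smoke.

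- 15 app, 5 control: 60/85 = 70.6% versus 85/95 = 89.5%, difference 18.9 points.
- 5 app, 15 control: 70/95 = 73.7% versus 75/85 = 88.2%, difference 14.6 points.

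The direction depends on which arm loses more.

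**5. No true effect.** 100 per arm, a fixed number of smokers removed, pooled z-test at two-sided 10%, exact enumeration.

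| Smoking in both arms | Excluded, app vs control | Analysed rates | Rejection |
|---|---|---|---|
| 90% | 0 vs 0 | 90.0% vs 90.0% | 10.2% |
| 90% | 10 vs 5 | 88.9% vs 89.5% | 10.8% |
| 90% | 15 vs 5 | 88.2% vs 89.5% | 11.9% |
| 80% | 0 vs 0 | 80.0% vs 80.0% | 9.9% |
| 80% | 15 vs 5 | 76.5% vs 78.9% | 13.6% |

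Reversing the imbalance gives the same rejection rates, with the excess against the app. Equal exclusion creates no difference between arms under the null.

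**6. Power with all 200 analysed.** Exact, 100 per arm, same test.

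- 75% versus 90% in all 200, with complete data: 88.5%.
- 75/90 in those followed, 22.5% missing and counted as smokers: 0.225 + 0.775×0.75 = 80.6% and 0.225 + 0.775×0.90 = 92.3%, power 78.9%.
- For comparison, 155 evaluable (77 and 78) at 75/90: 80.8%.

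**7. Counting missing as smoking is not neutral.** If 15% are missing in one arm and 30% in the other, unrelated to smoking, and 75% smoke in both, the rates become 0.15 + 0.85×0.75 = 78.8% and 0.30 + 0.70×0.75 = 82.5%. The 10% test then rejects about 17% of the time.

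**The case against.** The strongest reply has four parts.

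- **No set is assigned.** A reader might infer that the primary comparison will be run on LDCT attenders. The protocol does not say so. That is an inference from the only set in section 17, and linking sets to endpoints is often left to an SAP, which is not shown. This stands. But the protocol does define its populations, and it gives the ITT label to a set that is not all-randomised. An SAP could put this right only by departing from sections 6 and 17.1.
- **The section 6 set is close to everyone randomised.** A reader might infer that the receipt condition removes many subjects. It does not: all get the written material at the randomisation visit, and section 7.1 randomises only eligible subjects. What remains is the removal of subjects later found ineligible. This stands, and the LDCT condition is the material one.
- **The bias may be small.** Both arms have the same scan schedule, and subjects join a trial that offers the scan. It is tempting to put the 22.5% into the formula in step 3 and report 0.15/0.775 = 19.4 points. The documents do not support that: 22.5% is the implied overall dropout, not scan non-attendance, and an outcome lost at a call is a problem for any analysis set. A split such as 30% versus 15% has no source in the protocol either.
- **There is a rationale.** Section 3 asks about subjects undergoing LDCT screening, and section 1.3 argues that screening itself encourages cessation. That explains why the set exists. It does not justify selecting on attendance after allocation.

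**Conclusion.** The point holds as a defect in the definitions. The one population in section 17.1 depends on a post-randomisation scan that the primary outcome does not need, the section 6 ITT is not all-randomised, and no text settles which applies to the 3- and 6-month smoking comparison. If section 17.1 is followed, randomised subjects with known outcomes can be dropped.

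The size is unknown, because the protocol gives no non-attendance rate. Under the assumption that every excluded subject smokes, equal exclusion of 5% to 10% moves a true 15-point effect to 15.8 to 16.7 points. An imbalance of 10 versus 5 up to 15 versus 5 per 100 moves a nominal 10% error to between about 11% and 14%. These effects are modest against the design difference, and an imbalance can favour either arm. It cannot be concluded that the comparison will be biased, or that it must favour the app.

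**What to change.** In sections 6 and 17.1, define ITT as all randomised subjects analysed in the arm assigned, regardless of LDCT attendance, app use or later eligibility findings. Name it as the set for the primary smoking outcomes and for the secondary outcomes on reduction in smoking. Keep the set with at least one LDCT for the CT-screening outcomes only.

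Treat the handling of missing smoking status as a separate decision. If missing is counted as smoking, add a sensitivity analysis, since that rule also biases when missingness differs between arms (step 7).

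The cost is protocol wording, best changed before the primary analysis. No extra subjects or data are needed. With all 200 analysed, power is about 79% even if 22.5% are missing and counted as smokers, provided 75/90 holds in those followed.

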### 17.2 Analysis of Outcome Measures

#### 17.2.1 Primary Outcomes

- The percentage of subjects who are actively smoking at 3 months after inclusion between the study arms
- The percentage of subjects who are actively smoking at 6 months after inclusion between the study arms

Eligible subjects are randomized (1:1) with stratification according to pack years (<30py or ≥30py), and age (<65 or ≥65v) to smartphone based smoking cessation and control arm.

The study is powered (80%) with 155 subjects to detect 15% difference in (75 vs. 90%) in the number of active smokers at three and six months after inclusion with 90% confidence. With the expected dropout rate, the sample size is adjusted to 200.

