### Statistical Methods

Eligible subjects are randomized (1:1) with stratification according to pack years ( $<30py$  or  $\geq 30py$ ), and age ( $<65$  or  $\geq 65v$ ) to smartphone based smoking cessation and control arm.

The study is powered (80%) with 155 subjects to detect 15% difference in (75 vs. 90%) in the number of active smokers at three and six months after inclusion with 90% confidence. With the expected dropout rate, the sample size is adjusted to 200.

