#### 2.1.4 Outcome Measures

##### *Primary outcome measures*

- The percentage of subjects who are actively smoking at 3 months after inclusion between the study arms
- The percentage of subjects who are actively smoking at 6 months after inclusion between the study arms

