### 3. TRIAL DESIGN

This is a prospective randomized two arm Phase II trial to evaluate efficiency of different smoking cessation methods in subjects undergoing LDCT screening for lung cancer (Figure 1). For each subject, the trial will consist of a screening period (maximum four weeks) and intervention phase (for ~1y +/- 3 months). Survival data will be collected beyond the subject's active participation in the trial. The collection of the survival data of a subject is limited to 3 years from the randomization.

The primary objective of the trial is to assess the percentage of subjects who are actively smoking at 3 and 6 months after randomization.

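### The sample size fits one comparison but serves two equal primary time points, so the stated 80% power and 10% level hold for each endpoint and not for the trial

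*Protocol*

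**What the plan says.** Section 17.2.1 lists two primary outcomes without ranking them: "The percentage of subjects who are actively smoking at 3 months after inclusion between the study arms" and "The percentage of subjects who are actively smoking at 6 months after inclusion between the study arms". The same pair stands in the outcome lists of section 1 and section 2.1.4. Section 3 merges them into one objective: "The primary objective of the trial is to assess the percentage of subjects who are actively smoking at 3 and 6 months after randomization".

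One power statement, in the Statistical Methods part of section 1 and again in 17.2.1, serves both. It opens "The study is powered (80%) with 155 subjects to detect 15% difference in (75 vs. 90" (the last two figures are percentages) and continues "in the number of active smokers at three and six months after inclusion with 90% confidence". It is followed by "With the expected dropout rate, the sample size is adjusted to 200"; the dropout rate itself is not given. Randomisation is 1:1.

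The protocol does not say whether one or both time points must succeed, and it names neither the test nor its sidedness. Section 17.3 covers only when the analyses are done.

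**The concern.** Power and confidence are stated once, for two comparisons, with a number of subjects that looks like the size for one. If a difference at either time point makes the trial positive, there are two chances of a false positive at a level that is already lenient for a single test. If both time points must show a difference, the chance of success is lower than the chance for each alone. Either way, a reader who takes 80% and 90% as properties of the trial would be misled. Until the roles of the two time points are fixed, it is also open what would count as a positive trial. Section 17.4 sharpens this, because it allows efficacy analyses on an ongoing basis to support publication.

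**Working it through.** **Inputs from the protocol (17.2.1).** Proportions smoking 0.75 and 0.90; power 80%; 1:1 allocation; 155 subjects before dropout, 200 after. The level of 0.10 is inferred from 90% confidence.

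**Input assumed.** The correlation ρ between the 3- and 6-month test statistics is not in the documents. It is varied from 0 towards 1, with 0.4 to 0.8 as the working range. The true difference is taken as 75% versus 90% at both time points, as the power statement implies.

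**Step 1: reproduce 155.** For one two-sided 10% test, z = 1.645 for the level and 0.842 for the power.

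- Pooled variance: n per arm = [1.645·√(2·0.825·0.175) + 0.842·√(0.1875 + 0.09)]² / 0.15² = 78.3, rounded up to 79, so 158 in total.
- Unpooled variance: (1.645 + 0.842)²·0.2775 / 0.15² = 76.3 per arm, or 152.5 in total.
- Arcsine: 75.9 per arm, or 151.7 in total.
- Power at 155 (77.5 per arm): standard error 0.0610 under no difference and 0.0598 under the alternative, so m = (0.15 − 1.645·0.0610)/0.0598 = 0.829 and Φ(m) = 79.6%.

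Other conventions do not fit: two-sided 5% gives 200, one-sided 10% gives 114, and two-sided 10% with continuity correction gives 184. So 155 is the size for a single two-sided 10% test (numerically the same as one-sided 5%). It holds no allowance for a second primary endpoint. The step from 155 to 200 is dropout only: 1 − 155/200 = 22.5%.

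**Step 2: error rate if either time point counts.** Two-sided: 1 − P(|Z₁| < 1.645 and |Z₂| < 1.645). In favour of the app only: 1 − Φ₂(1.645, 1.645; ρ). With ρ = 0 these are 1 − 0.90² = 19.0% and 1 − 0.95² = 9.75%.

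**Step 3: power if both are required.** Φ₂(m, m; ρ), with m = 0.829 at 155 analysed and m = 1.170 at 200 analysed. With ρ = 0 these are 0.796² = 63.4% and 0.879² = 77.3%.

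| ρ (assumed) | Either: false positive, two-sided | Either: false positive favouring the app | Both: power, 155 analysed | Both: power, 200 analysed |
|---|---|---|---|---|
| 0 | 19.0% | 9.8% | 63.4% | 77.3% |
| 0.4 | 18.1% | 9.1% | 67.1% | 79.3% |
| 0.5 | 17.6% | 8.8% | 68.2% | 80.0% |
| 0.7 | 16.1% | 8.0% | 70.8% | 81.7% |
| 0.8 | 15.1% | 7.5% | 72.5% | 82.8% |
| 0.9 | 13.6% | 6.8% | 74.6% | 84.3% |
| limit 1 | 10% | 5% | 79.6% | 87.9% |

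**Step 4: what other rules would need.** Requiring both time points with 80% power takes about 200 analysed at ρ = 0.5 and 186 at ρ = 0.8. At 22.5% dropout that is about 258 and 240 enrolled. Splitting the level (two-sided 5% each) leaves 69.4% power per endpoint at 155 and needs 200 analysed for 80%.

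**The case against.** The strongest reply is that the power statement can be read endpoint by endpoint: 80% to detect the difference at 3 months, and 80% at 6 months. On that reading it is correct, as Step 1 shows. This stands. A reader might infer that the statement is false however it is read; the documents do not support that.

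Second, a rule for multiple endpoints may sit in an SAP that is not shown, so its absence from the protocol is no fault in itself. This also stands, but it does not settle the point. The protocol itself ranks the two endpoints equally and sizes both with a one-test number. An SAP that required both, or split the level, would not have 80% power at 155. An SAP that ranked them would depart from the protocol's two equal primaries.

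Third, a reader might infer that a false claim for the app has a probability of 15% or more. It does not: the two-sided rate also counts false findings against the app, and the rate in its favour is about half as large.

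Fourth, the loss of joint power is stated at 155 analysed. Section 17.1 defines the efficacy population by randomisation and at least one LDCT, so more than 155 may be analysed. With all 200, joint power is about 79-83% for ρ of 0.4 to 0.8.

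Finally, both time points are pre-specified, so a report that gave only the better one would visibly depart from the protocol.

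**Conclusion.** The point holds in a limited form. The stated 80% and 10% are right for each endpoint and not for the trial as a whole. For any correlation below 1, the trial-level two-sided error exceeds 10% if either time point counts: at most 19%, and about 15-18% for ρ of 0.4 to 0.8. In favour of the app it is about 7.5-9% instead of 5%. If both are required, power at 155 analysed is between about 63% and 80% (about 67-73% for ρ of 0.4 to 0.8).

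These sizes rest on the assumed correlation and on reading 90% confidence as a two-sided 10% level, which is the reading that reproduces 155. This should be fixed, since it decides what counts as a positive trial. It is not an arithmetic error in the sample size, and it does not invalidate the design.

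**What to change.** In sections 1, 2.1.4, 3 and 17.2.1:

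- Name active smoking at 6 months as the primary endpoint, tested first at two-sided 10%. Test 3 months at two-sided 10% only if the 6-month result is significant. This fixed order keeps the overall two-sided level at 10%.
- State that 80% power with 155 evaluable subjects refers to the 6-month test.
- State that the 6-month smoking status is recorded before a control subject is given the app. Sections 7.2 and 10.1 offer controls the app after six months, so a late call could otherwise follow that access.
- Reconcile the windows for the 3- and 6-month calls: one month either way in section 1 (Intervention Schedule), Table 1 and the text after Figure 3, but two weeks either way in section 7.2.1.

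The cost is wording, with no extra subjects, and the change should be made before outcome data are seen. The real price is that an effect at 3 months only can no longer be claimed as a primary success. The 3-month test also has to wait for the 6-month result, and the chance of winning both is the joint power shown above.

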#### 17.2.2 Secondary Outcomes

- The percentage of subjects who have reduced the amount of smoked cigarettes/d at 3 and 6 months after inclusion between the study arms
- The magnitude and percentage of reduction in cigarettes consumed/d at 3 and 6 months after inclusion between the study
- Sensitivity and positive predictive value of CT-screening in the whole cohort
- Costs related to CT screening including additional investigations

#### 17.2.3 Exploratory Outcomes

- Specificity of CT-screening in the whole cohort
- Lung cancer incidence (stage specific) and survival
- Number of additional CT-scans, PET-CT scans, bronchoscopies, needle biopsies, and their results (positive vs. negative for cancer) initiated based on screening CT-findings
- Percentage of subjects identified through newspaper advertisement and referral from primary care physician or occupational health physician
- Quality of life (QoL)
- Spectrum and grading of ePRO symptoms
- Correlation of ePRO symptoms to CT screen results
- Biomarker analysis of blood such as ctDNA
- AI-based evaluation of LDCT scans

